### Recruitment

A parent/guardian of an eligible infant will be approached by the coordinating principal investigator (CPI) or the CPI delegate and invited to participate in this study. Informed parental consent for trial participation will be required before elective surgical procedures are performed so that the trial intervention and data collection can be initiated.

## Assignment of interventions

### Random sequence generation

Group assignment will be allocated by the Clinical Trial Pharmacist at PCH using a computer-generated randomization sequence to minimize selection bias.

### Allocation concealment

Concealment will be obtained using opaque sealed envelopes. Once consent is obtained, a nursing staff member will open the next opaque sealed envelope to allocate the infant to the control or intervention group.

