### Study design, setting and time period

This prospective, parallel, single-center randomized controlled trial will be conducted in the neonatal ICU of Perth Children's Hospital (PCH), Child and Adolescent Health Service (CAHS), Perth, Australia. The PCH neonatal ICU is a 30-bed tertiary referral center that provides intensive and high dependency care for critically ill neonates. Over 800 infants are admitted to the PCH neonatal ICU each year, and all infants are born at other hospitals. This study has been approved by the CAHS Human Research Ethics (HREC) and Governance Committees and is on the Australian New Zealand Clinical Trials Registry. The study will aim to recruit eligible patients (n = 60) from July 2023 to July 2024. Newborns’ parents or guardians will be approached, and written informed consent will be obtained. The assessment plan is shown in table 1. This clinical protocol has been prepared according to the SPIRIT 2013 Checklist.^(12)^

**Table 1 t1:** Assessment plan

Informed consent
Inclusion/exclusion criteria review
Randomization
Measurement of the radial artery diameter by ultrasound preintervention by a blinded operator
Application of the GTN patch/bandage with no patch by unblinded nursing staff (not involved in the day-to-day management of the baby) for 30 minutes or 45 minutes or 60 minutes
Blood pressure measurement performed by the bedside nurse every 15 minutes until the end of the intervention
Tracking of oxygen saturation and FiO_2_ requirements by the bedside nurse
Blood gas measurement by the bedside nurse postintervention to measure methemoglobin levels
Removal of the GTN patch/bandage with no patch by unblinded nursing staff (not involved in the day-to-day management of the baby) for 30 minutes or 45 minutes or 60 minutes
Measurement of the radial artery diameter by ultrasound postintervention by a blinded operator

GTN - glyceryl trinitrate; FiO_2_ - fraction of inspired oxygen.

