### Participant withdrawal criteria

The mean and systolic blood pressure will be recorded every 15 minutes in both the GTN and Control Groups until the intervention ends. If any participant in either the GTN Group or Control Group develops hypotension (defined as a > 30% drop in systolic blood pressure from baseline) and/or any sudden increase in the oxygen requirement with an increase in the methemoglobin levels (determined by blood gas analysis), they will be removed from the study. Participants can withdraw from the study at any point.

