### Outcomes

#### Primary outcome:

the primary outcome will be the change in the postintervention radial artery diameter from baseline. This will be compared between the GTN and Placebo Groups.

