### Participant timeline

The study schedule is shown in table 1.

Duration of participant participation: 30 minutes to 1 hour.

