### Statistical methods

Table 3 gives a description of the timing and method of assessment of the efficacy and safety parameters. The ultrasound operator and examiner will be blinded to the study.

**Table 3 t3:** Timing and method of assessment of the efficacy and safety parameters

		Measured by	Analysis
Primary efficacy outcome			
	Change in postintervention ipsilateral radial arterial diameter from baseline	Ultrasound at the site of cannulation measured at time of randomization of glyceryl trinitrate/placebo patch and 30, 45 or 60 minutes postintervention	ANCOVA
Secondary outcomes			
	Cross-sectional radial artery diameter in the ipsilateral limb	Measured postintervention by ultrasound	Linear regression
	Percentage change from baseline in radial arterial diameter in ipsilateral limb	Ratio of the postintervention to baseline radial arterial diameters as measured by ultrasound	Linear regression
	Change in the radial artery diameter in the contralateral (no intervention) limb from baseline	Difference and ratio of the radial artery diameter measured at baseline and postintervention	Mixed effects regression modeling of radial artery diameters in both limbs.
Safety outcomes			
	Blood pressure	Systolic blood pressure monitored every 15 minutes	Mixed effects regression modeling of patient trajectories
	Methemoglobinemia	Monitoring of the oxygen requirement and a blood gas analysis if the oxygen requirement increases	Mixed effects regression modeling of patient trajectories

ANCOVA - Analysis of covariance.

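### Randomisation is placed before the baseline ultrasound, so an infant without a usable baseline scan can be lost after randomisation with no primary outcome

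*Protocol article*

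**What the plan says.** Three places in the protocol article bear on when an infant is randomised.

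- **Allocation concealment** ties the envelope to consent: "Once consent is obtained, a nursing staff member will open the next opaque sealed envelope to allocate the infant to the control or intervention group".
- **Table 1** (Study design, setting and time period) lists, in this order, consent, "Inclusion/exclusion criteria review", randomisation, "Measurement of the radial artery diameter by ultrasound preintervention by a blinded operator", and then application of the patch or bandage.
- **Table 3** (Statistical methods) has the ipsilateral diameter "measured at time of randomization of glyceryl trinitrate/placebo patch and 30, 45 or 60 minutes postintervention".

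Under Primary outcome, "the primary outcome will be the change in the postintervention radial artery diameter from baseline", so both a baseline and a post-intervention scan are needed. Under Recruitment, "Informed parental consent for trial participation will be required before elective surgical procedures are performed", with no interval given between consent and the trial procedures. The Participant timeline reads "Duration of participant participation: 30 minutes to 1 hour". The Sample size section recruits 60 infants, 15 in each of four arms, and bases its power statement on the same 15 per arm.

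**The concern.** None of the three places puts the baseline scan first. Two put randomisation ahead of it and the third makes them simultaneous. The scan can fail: the Sample size section assumes a mean diameter of 0.76 mm, in a newborn who may not lie still. If the envelope is already open when the operator finds that no usable image can be had, the infant has been randomised but cannot have a change from baseline. Had the scan come first, the same infant would have been a screening failure and would have cost the trial nothing.

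There is a second, weaker route. If an infant is consented well ahead of elective surgery and the envelope is opened at consent, the infant could meet an exclusion criterion, such as hypotension or a radial cannulation attempt, before the patch or bandage is applied.

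What is at stake is mainly the precision of a small trial that recruits no more infants than its power statement uses.

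**Working it through.** **Inputs, all from the Sample size section:** four groups (one control, three GTN) of 15; control mean 0.76 mm; common SD 0.18 mm; minimum difference from control 0.19 mm; alpha 0.05; one-way ANOVA omnibus test; stated power more than 80%.

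**Step 1: reproduce the stated power.** Put all three GTN arms at the minimum difference, so the means are 0.76, 0.95, 0.95 and 0.95 mm. This is the least favourable pattern in which every GTN arm gains at least 0.19 mm.

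- Grand mean relative to control: 3 × 0.19 / 4 = 0.1425 mm.
- Sum of squared deviations: 0.1425² + 3 × 0.0475² = 0.027075.
- Noncentrality: λ = n × 0.027075 / 0.18² = 15 × 0.027075 / 0.0324 = 12.53.
- Degrees of freedom: 3 and 4 × 15 − 4 = 56. Critical F = 2.77.
- Power from the noncentral F distribution: 83.0%. The article's figure reproduces.

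**Step 2: remove infants who have no baseline.** The article gives no loss rate. The assumed range is one to three infants per arm, which is 1/15 = 7% to 3/15 = 20%. Same formula, smaller n:

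| Lost per arm (assumed) | n per arm | λ | df | Omnibus power |
|---|---|---|---|---|
| 0 | 15 | 12.53 | 3, 56 | 83.0% |
| 1 | 14 | 11.70 | 3, 52 | 79.8% |
| 2 | 13 | 10.86 | 3, 48 | 76.2% |
| 3 | 12 | 10.03 | 3, 44 | 72.0% |

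**Step 3: a comparison that is less sensitive.** Pooling the three GTN arms against control (45 v 15, two-sided t test, same difference and SD) gives 93.6% with no loss. With one, two or three lost per arm it gives 91.9%, 89.8% and 87.3%.

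**Step 4: the price of keeping the present order.** To end with 60 analysable infants, the number randomised must be 60 / (1 − d), rounded up. That is 64 at d = 5%, 67 at 10%, 71 at 15% and 75 at 20% (assumed rates).

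**The case against.** The best reply is that the article describes a single bedside session. Requiring consent before the envelope is opened does not mean opening it at the moment of consent. Table 1 puts an eligibility review between the two, Table 3 ties the baseline scan to randomisation, participation lasts at most an hour, and one nurse both opens the envelope and applies the patch or bandage. This stands for most infants. It makes the changed-clinical-course route depend on a literal reading of the Allocation concealment sentence for infants consented early. It does not remove the failed-scan route, because an eligibility review does not test whether the artery can be measured.

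Two points on size also stand. The power statement concerns cross-sectional diameter, and the article expects the change-from-baseline analysis to do better; by how much cannot be computed, since no within-infant correlation is given. The pooled comparison also keeps ample power.

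A reader might infer more than the documents support:

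- **Bias.** Losses before application, judged by a blinded operator, should not depend on arm.
- **Leakage of the allocation into the baseline scan.** The nurse who knows it has no other part in the study, nothing is yet on the wrist, and no route to the operator is described.
- **Damage to the control subgroups of five.** The Sample size section treats control as one group of 15, and no stated analysis compares the subgroups.
- **That reordering would bring losses close to zero.** Failed post-intervention scans remain, as do infants with hypotension, or with a raised oxygen requirement and methemoglobin, for whom "they will be removed from the study".

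**Conclusion.** The point holds as an avoidable weakness in the order of procedures, not as a demonstrated loss of infants. As written, randomisation comes before or at the same time as the baseline scan that the primary outcome needs, and the recruitment target has no margin. The size is unknown because no failure rate is given. If one infant per arm were lost, the omnibus power would fall from 83.0% to 79.8%, just below the stated level; two or three per arm would take it to 76.2% or 72.0%. These figures assume equal losses across arms, all GTN arms at +0.19 mm, and the cross-sectional SD of 0.18 mm. They probably overstate the effect on the change-from-baseline analysis. The early-consent route adds to the risk only if envelopes are in fact opened at consent.

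**What to change.** Align three places in the protocol article.

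1. **Allocation concealment:** state that the envelope is opened only after consent, confirmation of eligibility on the day, and acquisition and saving of the baseline scans of both radial arteries, immediately before the patch or bandage is applied.
2. **Table 1:** move the randomisation row below the baseline ultrasound row.
3. **Table 3:** describe the baseline measurement as taken before randomisation.

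If the present order is kept, add a loss allowance to the recruitment target using the arithmetic above.

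**Cost:** one sentence, one table row and one table entry. Staff and tasks do not change. A few infants will be scanned and never randomised, and the Ethics and dissemination section means that the change needs prior ethics committee approval.

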### Blinding

Blinding of families, health care providers and study investigators to the group allocation will be performed.

#### Unblinded staff:

a nursing staff member who is not involved in the day-to-day management of the neonate will be responsible for opening the envelope, determining the group assignment and applying the GTN patch/placebo and removing the GTN patch/placebo with no additional participation in the study.

#### Blinded staff:

the ultrasound measurements of the radial artery will be performed by an operator who will be blinded to the intervention. In addition, the bedside nurse who measures the blood pressure every 15 minutes until the end of the intervention will also be blinded.

There will be a blinded and unblinded delegation log for blinded and unblinded trial members with their duties listed.

## Data collection, management, and analysis

### Data collection methods

All clinical data, such as patient characteristics, including gestational age, chronological age, sex, weight, location, main diagnosis, vital signs, medications, and ventilation use, will be collected (Table 2).

**Table 2 t2:** Patient and clinical characteristics

		GTN Group n = 45	Control Group n = 15
Birth weight			
Gestational age			
Date of birth			
Sex			
	Male		
	Female		
Age at intervention			
Diagnoses			
	Perioperative		
	Medical		
Medications			
	None		
	Antibiotics		

GTN - glyceryl trinitrate.

After obtaining informed consent from each patient's parent, images of the radial artery will be obtained from the infant's wrist using a portable ultrasound machine. The diameter of the radial artery will be measured using a linear, high-frequency hockey stick probe (6 - 13MHz) with the Philips EPIQ CVx Diagnostic Ultrasound system.

The operator will be an experienced neonatologist (member of the Australian Society for Ultrasound in Medicine and routinely performing ultrasounds in the unit) who is blinded to the study group. Measurements will be obtained in the radial arteries of both limbs at baseline before application of the GTN patch/bandage with no patch and at 30 minutes, 45 minutes or 60 minutes after application.

### Data management

The trial involves the collection of clinical data and radial artery images by ultrasound measurement. They will be stored in a password-protected database on the hospital computer. CAHS health department information technology will be involved to help secure these data in a password protected system. Sharing or reuse of data will not be performed. Records will be stored in a locked filing cabinet in a secured office in Neonates at Perth Children's Hospital. The study data will be retained per the Western Australia health guidelines. Data collected will be accessed only by the authorized members of the study team named on the HREC application for the study.

### Statistical methods

Table 3 gives a description of the timing and method of assessment of the efficacy and safety parameters. The ultrasound operator and examiner will be blinded to the study.

**Table 3 t3:** Timing and method of assessment of the efficacy and safety parameters

		Measured by	Analysis
Primary efficacy outcome			
	Change in postintervention ipsilateral radial arterial diameter from baseline	Ultrasound at the site of cannulation measured at time of randomization of glyceryl trinitrate/placebo patch and 30, 45 or 60 minutes postintervention	ANCOVA
Secondary outcomes			
	Cross-sectional radial artery diameter in the ipsilateral limb	Measured postintervention by ultrasound	Linear regression
	Percentage change from baseline in radial arterial diameter in ipsilateral limb	Ratio of the postintervention to baseline radial arterial diameters as measured by ultrasound	Linear regression
	Change in the radial artery diameter in the contralateral (no intervention) limb from baseline	Difference and ratio of the radial artery diameter measured at baseline and postintervention	Mixed effects regression modeling of radial artery diameters in both limbs.
Safety outcomes			
	Blood pressure	Systolic blood pressure monitored every 15 minutes	Mixed effects regression modeling of patient trajectories
	Methemoglobinemia	Monitoring of the oxygen requirement and a blood gas analysis if the oxygen requirement increases	Mixed effects regression modeling of patient trajectories

ANCOVA - Analysis of covariance.

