## Methods/Design

### Aim and hypothesis

We aim to conduct a randomized controlled trial to establish the effectiveness of local GTN in increasing the diameter of the radial artery in neonates.

We hypothesize that local application of GTN in the form of a transdermal patch will result in adequate dilation (by at least 25% from the baseline diameter) of the radial artery in neonates.

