#### Secondary outcomes:

the secondary outcomes will be the postintervention cross-sectional radial artery diameter in the ipsilateral limb and the percentage change in the radial arterial diameter in the ipsilateral limb from baseline. Postintervention absolute and percentage changes in the radial arterial diameter in the contralateral limb from baseline will also be assessed.

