### Sample size

We aim to recruit 60 patients (15 in each arm: 1 control and 3 GTN arms) over 12 months, which is achievable given that we expect approximately 250 eligible patients to be admitted to the neonatal ICU each year.

Justification of the sample size is based on the desire to demonstrate that reasonable vasodilation with GTN patch application is achievable in our target study population. We assume that the measures of the radial artery diameter in study participants will have a mean of 0.76mm without treatment and a common within-group standard deviation of approximately 0.18mm, as observed in a reference study of neonates aged 0 - 6 months.^(12)^ With a sample size of 15 for each group (1 control and 3 GTN patch groups), the margin of error around the corresponding estimated population mean diameters is less than 1 mm, and an omnibus one-way ANOVA would have more than 80% power to determine whether GTN patch application increases the radial artery diameter when the minimum mean of the treatment group differs from that of the control group by approximately 0.19mm (alpha = 0.05). Analyses based on the change from baseline, which is our primary outcome, are expected to be more powerful than analyses assessing the cross-sectional diameters, and the detectable cross-sectional difference of 0.19mm corresponds to an approximate 25% increase from the estimated baseline value, which is of the order previously observed in children aged 0 - 2 years receiving subcutaneous injections of GTN,^(11)^ and substantially less than that observed after patch application in children aged 2 - 8 years (average increase of 40% in the radial artery diameter after 30 minutes and an increase of 70% after 1 hour).^(10)^ Furthermore, power will be increased by extending the assessment of GTN-induced vasodilation to an ANCOVA that reduces residual variation by adjusting for key demographic/clinical correlates of arterial diameter.

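### The secondary percentage-change outcome is planned as a linear regression of a post/baseline ratio with no baseline covariate or log scale named: valid, but less efficient than a baseline-adjusted model

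*Protocol article*

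**What the plan says.** All references are to the protocol article.

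- **Statistical methods, Table 3.** The secondary outcome "Percentage change from baseline in radial arterial diameter in ipsilateral limb" is measured as the "Ratio of the postintervention to baseline radial arterial diameters as measured by ultrasound". Its analysis entry is "Linear regression" and nothing more. The primary outcome in the same table is labelled ANCOVA.
- **Secondary outcomes.** The text lists "the percentage change in the radial arterial diameter in the ipsilateral limb from baseline".
- **Aim and hypothesis.** The hypothesis is put on the relative scale: "adequate dilation (by at least 25% from the baseline diameter) of the radial artery in neonates".
- **Primary outcome.** This is on the absolute scale: "the primary outcome will be the change in the postintervention radial artery diameter from baseline".
- **Sample size.** Diameters "will have a mean of 0.76mm without treatment", with a within-group SD of about 0.18 mm and 15 infants in each of four groups. The section also foresees an ANCOVA adjusting for demographic and clinical correlates of diameter; baseline diameter is not named among them. No correlation between baseline and postintervention diameter is given.

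**The concern.** A post/baseline ratio is not free of baseline. When the two measurements are imperfectly correlated, infants with a small baseline diameter tend to show a large ratio and those with a large baseline a small one. In simulated controls the ratio correlates between about -0.47 and -0.30 with baseline when the pre-post correlation is 0.5 to 0.8. If the model leaves baseline out, that variation stays in the residual, and with only 15 controls it costs precision. The ratio is also right-skewed, and under proportional dilation its spread is larger in the treated groups.

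At stake is the precision of the row that speaks most directly to the 25% hypothesis, and that sits on the scale of the percentages from earlier studies cited in the Sample size section. Baseline diameter is measured in every infant, so the information needed to recover the precision is already collected.

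**Working it through.** **Inputs.** From the Sample size section: mean 0.76 mm, SD 0.18 mm, four groups of 15 (45 GTN, 15 control), alpha 0.05, difference 0.19 mm. From Aim and hypothesis: 25% dilation. Assumed: the pre-post correlation r, lognormal diameters and a proportional treatment effect.

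**Step 1: the plan's own figure.** 0.19/0.76 = 25%. For the omnibus F test with group means (0, 0.19, 0.19, 0.19), the sum of squared deviations is 0.1425² + 3 × 0.0475² = 0.027075. Lambda = 15 × 0.027075/0.18² = 12.5 on 3 and 56 df, and power is 83.0%. This agrees with the stated figure of more than 80%. It concerns cross-sectional diameter in mm and does not involve the ratio.

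**Step 2: plausible correlations.** A simple change score has variance 2σ²(1 − r), which is below the cross-sectional σ² only if r > 0.5. The Sample size section expects change from baseline to be the more powerful analysis. Read as a simple change score, that implies r above 0.5, so 0.5 is the low end.

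**Step 3: theory on the log scale.** Unadjusted log ratio: variance 2σ²(1 − r). Log postintervention diameter adjusted for log baseline: σ²(1 − r²). The quotient is 2/(1 + r): 1.33 at r = 0.5, 1.18 at 0.7, 1.11 at 0.8 and 1.05 at 0.9.

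Hand check at r = 0.5 and a 25% effect:
- Log SD = √ln(1 + (0.18/0.76)²) = 0.234; effect ln 1.25 = 0.223; √(1/45 + 1/15) = 0.298.
- Adjusted: SE = 0.234 × √0.75 × 0.298 = 0.060; 0.223/0.060 ≈ 3.70; normal-approximation power about 96%.
- Unadjusted log ratio: SE = 0.234 × 0.298 = 0.070; 0.223/0.070 ≈ 3.20; power about 89%.

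The simulated values for these two models are 95% and 88%.

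**Step 4: simulation of the 45 v 15 contrast.** Raw ratio on group, against log(post) on group and log(baseline), two-sided 5%:

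| r | 25% effect: ratio v log, adjusted | 15% effect: ratio v log, adjusted |
|---|---|---|
| 0.5 | 87% v 95% | 48% v 62% |
| 0.7 | 98% v 99% | 70% v 79% |
| 0.8 | no difference | 87% v 92% |

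The 15% column is for sensitivity only; the protocol's target is 25%.

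**Step 5: source of the gain.** One set of runs at r = 0.5 and a 25% effect gave: raw ratio 86.2%, log ratio without baseline 88.2%, raw ratio plus baseline 93.5%, log model with log baseline 95.0%. The baseline covariate alone recovers 93.5 − 86.2 = 7.3 of the 95.0 − 86.2 = 8.8 points; the log alone recovers 2.0.

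**Step 6: validity.** Type I error of the raw-ratio regression lay between 4.3% and 5.4% in all runs. Coverage of its 95% interval was 95% under the null and 96% to 97% at effects of 15% or 25%. At a 25% effect the mean pooled SE was 0.086 against a true sampling SD of 0.078 at r = 0.5 (0.086/0.078 = 1.10), and 0.053 against 0.048 at r = 0.8 (also 1.10). The larger variance sits in the larger group, so the error is conservative.

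**Step 7: four-group F test.** If the row were tested across all four groups, the loss at a 25% effect would be larger. On lognormal data power is 70% v 86% at r = 0.5, 91% v 96% at 0.7 and 98.9% v 99.4% at 0.8. With normal data and an additive effect it is 66% v 92%, 88% v 98% and 97% v 99.9%.

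**The case against.** The strongest reply is that Table 3 does not say that the ratio is unlogged or that group is the only term. Linear regression of the log ratio with log baseline as covariate fits the table's wording and gives exactly the group effect recommended here. A journal article commonly leaves transformation and covariates to the full protocol or SAP, neither of which is shown. This stands: the silence is not an error. What remains is that the table names a variable and a method, reserves the ANCOVA label for the primary row, and nowhere names baseline diameter as a covariate. The plain reading is therefore the less efficient model, and confirming or changing it is worthwhile.

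A reader might go further and infer that the ratio analysis is invalid, because its variance is unequal between groups or because a chance baseline imbalance distorts the estimate. The figures do not support that. Test size is about nominal and intervals are slightly too wide, not too narrow. Under randomisation a chance imbalance adds noise that the standard error already reflects; it is not bias.

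It can also be said that the log scale is largely a matter of preference and changes the estimand from a difference in mean ratios to a ratio of geometric means. Both are true. Most of the gain comes from the baseline term, which is why the fix offers a version without the log.

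**Conclusion.** The point holds as one of efficiency on a secondary outcome. Read plainly, the Table 3 regression of the ratio is valid but gives a less precise answer than the same data allow, on the scale of the 25% hypothesis. For the 45 v 15 contrast at that effect, the cost is about 8 percentage points of power at a correlation of 0.5, about 1 point at 0.7, and nothing at 0.8 or more. These sizes rest on correlations that the document does not give, and on lognormal data with a proportional effect.

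It would be tempting to conclude that the trial's power or its main result is compromised. The document does not support this: the primary outcome is absolute change analysed by ANCOVA, the sample size is set in mm, and its stated power reproduces at 83%. The point is a low-priority improvement.

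**What to change.** In the percentage-change row of Table 3, or in the SAP, specify a linear model of log(postintervention diameter) on group with log(baseline diameter) as covariate. Report the exponentiated group effect minus 1 as percentage dilation, with a 95% confidence interval. At minimum, add baseline diameter as a covariate to the ratio regression.

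The cost is one line of text and no new data. The only downside of the log model is that the estimate must be described as a ratio of geometric means. If the SAP already specifies such a model, a clarifying phrase in the table is enough.

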### Objectives

The specific objectives are:

To confirm that GTN patch application for 30 - 60 minutes increases the radial artery diameter of neonates.To confirm that it is safe to apply a GTN patch for 30 - 60 minutes for neonates.To estimate the mean values of the within-patient changes in the peripheral artery diameter from baseline to inform the choice of the optimal duration of GTN patch application in the context of cannulation in neonates.To evaluate the feasibility of a proposed future trial design to assess the impact of GTN patches on first-attempt cannulation rates in terms of recruitment and data collection.

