### Data and safety monitoring

An independent Data and Safety Monitoring Committee (DSMC) has been established to ensure the safety of the trial participants and to monitor the quality of the study and data collection. The DSMC has a neonatologist and senior pharmacist who are external to PCH and will not be involved in the trial. The DSMC will review the study data and conduct interim analyses following the recruitment of 20 and 40 participants for the key safety outcomes: the incidence of hypotension (defined as a decrease in systolic blood pressure by 30% from the baseline reading or more) and methemoglobinemia (as measured by blood gas analysis if any infant develops a sudden increase in their oxygen requirement after the intervention). The DSMC charter is enclosed as a supplemental file.

All adverse events will be reported to the HREC of CAHS and DSMC within one business day of the first report of the event.

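### Methemoglobin sampling is unconditional in Table 1 but triggered by a rise in oxygen requirement in Table 3 and the DSMC section, and the trajectory model named for it suits neither version

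*Protocol article*

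**What the plan says.** The protocol article describes methemoglobin measurement in four places.

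- Table 1 (Study design, setting and time period) has a line with no condition: "Blood gas measurement by the bedside nurse postintervention to measure methemoglobin levels". Oxygen monitoring is a separate line: "Tracking of oxygen saturation and FiO_2_ requirements by the bedside nurse".
- Table 3 (Statistical methods) gives the measurement of methemoglobinemia as "Monitoring of the oxygen requirement and a blood gas analysis if the oxygen requirement increases".
- Data and safety monitoring names the incidence of methemoglobinemia as one of two key safety outcomes, to be reviewed after 20 and 40 infants, "as measured by blood gas analysis if any infant develops a sudden increase in their oxygen requirement after the intervention".
- Participant withdrawal criteria refer to a sudden rise in oxygen requirement together with an increase in methemoglobin on blood gas.

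For analysis, Table 3 gives methemoglobinemia the same entry as blood pressure: "Mixed effects regression modeling of patient trajectories". No section schedules a baseline or repeated methemoglobin value. The second objective is "To confirm that it is safe to apply a GTN patch for 30 - 60 minutes for neonates". The allocation is "15 in each arm: 1 control and 3 GTN arms", that is 45 GTN and 15 control infants.

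**The concern.** There are two linked problems.

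The first is who gets measured. Staff following Table 1 and staff following Table 3 would collect different data. Under the triggered rule, an infant whose oxygen requirement does not rise has no methemoglobin value, yet would appear as a non-case in any incidence. A raised level without that sign could not be found. A low or zero count would then partly reflect the sampling rule.

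The second is how the outcome is analysed. A trajectory model needs repeated values of the same quantity in the same infant. Blood pressure, taken every 15 minutes, has them. Methemoglobin does not under either rule.

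What is at stake is the methemoglobinemia half of the safety objective, and what the monitoring committee can learn at its two reviews. The primary outcome, its ANCOVA, the sample size and the blood pressure data are not affected.

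**Working it through.** The article states no figure for methemoglobinemia, so there is none to reproduce.

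**Step 1: values per infant.**

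| Source | Scheduled baseline | Postintervention values |
|---|---|---|
| Table 1 | none | 1 |
| Table 3 and Data and safety monitoring | none | 0 unless the oxygen requirement rises |

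A trajectory needs at least 2. If both rules ran together, an infant with a trigger might have a routine and a triggered gas, but such infants would be few.

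**Step 2: can the model be fitted to one value per infant?** With a random intercept, the variance of a single value is the between-infant variance plus the residual variance, and only the sum can be estimated. As a check, 60 infants (45 and 15) were simulated with one value each (assumed mean 1, SD 0.3). The software warned that the Hessian was not positive definite and split the variance equally, 0.035 and 0.035. Its standard error for the group difference was 0.053, against 0.078 from ordinary regression on the same data. The estimate itself was the same, -0.019. A fit forced through software could therefore overstate precision.

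**Step 3: what zero cases would show.** Let p be the true incidence in GTN infants and s the share of cases that show a rise in oxygen requirement. The number of GTN infants is 3 x 15 = 45. The shares s are assumptions.

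- All sampled: the one-sided 95% upper limit U solves (1 - U)^45 = 0.05, so U = 1 - 0.05^(1/45) = 0.0644, or 6.4%.
- Triggered: the same 0/45 bounds p x s, so the limit on p is 0.0644 / s.
  - s = 0.5: 0.0644 / 0.5 = 12.9%.
  - s = 0.25: 0.0644 / 0.25 = 25.8%.

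**Step 4: chance of seeing at least one case among 45 GTN infants**, 1 - (1 - p x s)^45, with p and s both assumed:

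| p | All sampled | s = 0.5 | s = 0.25 |
|---|---|---|---|
| 2% | 0.60 | 0.36 | 0.20 |
| 5% | 0.90 | 0.68 | 0.43 |
| 10% | 0.99 | 0.90 | 0.68 |

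At p = 5% the expected number of cases seen is 45 x 0.05 = 2.25 with all sampled, 1.13 with s = 0.5 and 0.56 with s = 0.25. At the first committee review, if 15 of the 20 infants are in GTN arms, the chances at p = 5% are 0.54, 0.32 and 0.17.

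**The case against.** Table 1 is a terse list of steps. It does not literally say every infant, and the other three places all link methemoglobin to a rise in oxygen requirement, so its line may be shorthand for the triggered rule. That is possible. However, the line carries no condition and oxygen tracking is listed separately, so the unconditional reading is the natural one. The text needs settling either way.

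A reader might infer that the outcome is bound to be under-counted and cannot be estimated. The document does not support that. If Table 1 governs, each infant has one value, nothing is lost through triggering, and incidence by group follows from a simple comparison; only the named model fails. If the triggered rule governs, the incidence of methemoglobinemia with an oxygen rise is still estimable. The loss concerns cases without that sign, and the article gives no figure for how common they are.

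The model could also be meant for the tracked oxygen requirement. It could be fitted to that if enough readings are taken (Table 1 gives no frequency), but oxygen requirement does not measure methemoglobinemia.

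Finally, a committee reviewing incidence while the final analysis uses a model is not in itself a contradiction. Event counts by arm may also appear in a charter or analysis plan that is not shown. This stands, and the point does not rest on their absence. It rests on two sampling rules that differ and on a stated model that fits neither.

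**Conclusion.** The concern holds in a limited form. The protocol article contradicts itself on whether the methemoglobin gas is conditional, and the analysis in Table 3 does not suit the outcome under either reading.

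The consequence for incidence depends on which rule operates. Under the triggered rule, 0/45 supports an upper limit of 6.4% only for methemoglobinemia with an oxygen rise. For all methemoglobinemia the limit is about 12.9% or 25.8% at the assumed shares of one half and one quarter. These figures pool the three GTN arms, take all 45 infants as observed, and assume that every infant with an oxygen rise is sampled and that the gas detects a case when present. No particular incidence or share should be read into the protocol. Its dose justification reports no methemoglobinemia in the pediatric studies.

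**What to change.** 1. Reconcile Table 1, Table 3, Data and safety monitoring and the withdrawal criteria on who is sampled and when, and on what an increase in methemoglobin is measured against. Which rule applies is for the investigators to decide. The statistical consequence is that only sampling that does not depend on oxygen requirement supports an unbiased incidence by group.
2. In Table 3, replace the trajectory model for methemoglobinemia with the number and proportion per group and exact 95% confidence intervals, with the number sampled as the denominator. If one value per infant is collected, add a simple linear regression of that value on group. Keep the mixed model for serial blood pressure.
3. If the triggered rule is retained, name the outcome methemoglobinemia with increased oxygen requirement. Report it out of all infants monitored, state how many were sampled, and limit the safety conclusion to that outcome.

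The cost is wording and a simpler analysis. If unconditional sampling is confirmed, the gas is already in the Table 1 schedule. If practice has followed the triggered rule, confirming it would add a blood gas for infants without a trigger. The question should be settled before the first committee review, because values not taken cannot be recovered.
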